### Setting

10 clinics spanning five CHC systems have agreed to participate in this study*.* These include FQHCs and community-oriented primary care clinics affiliated with county safety-net systems (Table 1). Per power estimations, only 8 clinics are needed to test effectiveness. We selected CHCs with a high proportion of minority and under/uninsured individuals. In addition, the CHCs vary in size (5–15 clinicians) and geographic location (urban–rural continuum), allowing us to examine contextual factors influencing effectiveness and implementation [38, 39].

**Table 1 Tab1:** Patient characteristics of partner CHCs

Community Health Center *(Partner Clinics)*	% Racial/Ethnic Minorities	% Uninsured/Medicaid	Estimated # Survivors seen per year per clinic*
CHC1 (2 clinics)	83%	53%	139
CHC2 (2 clinics)	98%	58%	106
CHC3 (2 clinics)	92%	77%	176
CHC4 (2 clinics)	91%	77%	607
CHC5 (2 clinics)	93%	88%	1008

^***^*Estimated prevalence of 6.5% based on preliminary data* [29]

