### Quantitative data collection

#### EHR extraction/audit

The study team with support from clinic EHR specialists will extract EHR data for eligible patients at the end of every 6-month period. Extracts will include all patients with a history of cancer who were seen in the respective 6-month period.

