#### Power calculation

The primary outcome variable is continuous, for which Hussey and Hughes (2007) derived a closed-form analytical expression for power using linear mixed-effect model [34]. This formula is implemented in the PASS 2022 software, which is used for power calculation. From the historical records of recruitment feasibility, we propose to recruit 100 subjects (or more) per clinic in every six-month period. This results in a sample size N = 100*8*6 = 4800, out of which about 2000 will be under usual care and 2800 under intervention condition (excluding intervention implementation period in each clinic). We assume an ICC < 0.05 (within clinic association). We assume the difference in screening rate between intervention and usual care condition is ≥0.15 to guarantee ≥85% power, with a two-sided type-1 error of 0.05 (see power curve figure). Sample size using Heo et al. (2018) is slightly larger but still guarantees ≥ 80% power (checked using the swCRTdesign package in R software) [115]. A cross-sectional stepped wedge design assumes that outcomes are assessed for unique survivors every six months, and we recognize that eligible patients may return for regular clinic visits. However, for any eligible survivor, if the outcome of cancer screening in the past period is negative, then that past outcome does not affect the outcome of screening in the future period, and survivors who screened positive (in any period) are then not eligible for outcome assessment in future periods. The stepped-wedge design can be implemented in two forms: cross-sectional and repeated-measures. We have chosen a cross-sectional stepped-wedge design (open cohort), which assumes that clinics may evaluate new subjects during each observation window (i.e., every six months). While it is possible that a subject who screened negative in a previous period may return for screening in a later period (if still eligible), we expect the number of such repeat participants to be low. Importantly, for any given subject, a negative screening outcome in a previous period does not influence the likelihood of a positive outcome in a subsequent period. Subjects who screen positive in any period are referred for appropriate treatment and removed from future screening. Therefore, no sample size adjustment has been made for potential repeated observations within a clinic. Missing data is minimal in this cross-sectional design due to long-standing CHC relationships and ongoing partner engagement.

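### The sample size assumes few repeat patients, but Table 1 forces repeats at six of the ten clinics, and the reason given for no adjustment concerns test results rather than receipt of screening

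*Protocol article*

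**What the plan says.** The Power calculation section of the protocol article states that "we propose to recruit 100 subjects (or more) per clinic in every six-month period". It continues "This results in a sample size N = 100*8*6 = 4800", "out of which about 2000 will be under usual care and 2800 under intervention condition". It describes the design as cross-sectional with unique survivors assessed each half-year, and also labels it an open cohort. It accepts that some survivors may come back, but says "we expect the number of such repeat participants to be low" and concludes that "no sample size adjustment has been made for potential repeated observations within a clinic".

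Two reasons are offered. A negative screen in one period is said not to affect a positive screen later. And "survivors who screened positive (in any period) are then not eligible for outcome assessment in future periods"; these subjects are said to be referred for treatment.

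Three other places bear on this:

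- **Setting, Table 1.** The column "Estimated # Survivors seen per year per clinic" shows 139 (CHC1), 106 (CHC2), 176 (CHC3), 607 (CHC4) and 1008 (CHC5), with two clinics in each system.
- **Outcomes.** The primary outcome is the proportion of patients who have received guideline-concordant screening for second primary cancers.
- **EHR extraction/audit.** "Extracts will include all patients with a history of cancer who were seen in the respective 6-month period".

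The Data analysis section fixes a model with a clinic random effect, period fixed effects and an intervention indicator. It has no term for the patient.

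**The concern.** Two non-overlapping samples of 100 per year need 200 distinct survivors per clinic-year. Six of the ten clinics see fewer than that by the protocol's own table, so the sample size and the expectation of few repeats cannot both hold there.

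The argument for ignoring repeats also addresses a different variable from the primary outcome. A survivor who is screened with a negative result has met the outcome, is not removed, and can meet it again in a later period. Whether a person gets screened is plausibly persistent, so the independence that the sample size relies on is not established.

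At stake are the meaning of 4,800, the validity of the standard error for the primary test, and a clear definition of who is assessed in each period.

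**Working it through.** **1. The plan's own figures.** 100 × 8 × 6 = 4,800. With four sequences of two clinics crossing after periods 1, 2, 3 and 4, usual-care cells number (1+2+3+4) × 2 = 20, giving 2,000. Intervention cells number (5+4+3+2) × 2 = 28, giving 2,800. Both reproduce, so 4,800 is the sum of 48 clinic-period cells of 100.

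**2. Distinct survivors available.** The need per clinic is 6 × 100 = 600 over three years. The most generous case replaces every patient every year, so the ceiling is 3 × the Table 1 count. The minimum repeat share is (600 − ceiling)/600.

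| System | Per year | Short of 200 | Ceiling, 3 years | Minimum repeats |
|---|---|---|---|---|
| CHC1 | 139 | 61 | 417 | 183/600 = 31% |
| CHC2 | 106 | 94 | 318 | 282/600 = 47% |
| CHC3 | 176 | 24 | 528 | 72/600 = 12% |
| CHC4 | 607 | 0 | 1,821 | 0 |
| CHC5 | 1,008 | 0 | 3,024 | 0 |

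Only four clinics belong to CHC4 and CHC5, so any eight include at least four from CHC1–3. Capping each clinic at 600, the best choice (leaving out CHC2) has at most 2 × (417 + 528 + 600 + 600) = 4,290 distinct patients. The worst (leaving out two of the large clinics) has at most 2 × (417 + 318 + 528) + 2 × 600 = 3,726. These are upper limits. Anyone seen in more than one year lowers them.

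**3. The argument against the outcome.** The justification links a negative screen to a later positive screen. The outcome is screened or not screened. Independence of test results across periods says nothing about correlation of receipt across periods. Removing test-positive patients does not touch the larger group who were screened with a negative result and return.

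**4. Effect on the standard error.** Assumptions not in the protocol: screening rate p = 0.5, ICC at its stated bound of 0.05, and residual within-patient correlation 0.6. Then the clinic variance is 0.05 × 0.25 = 0.0125, and the residual variance of a cell mean is 0.95 × 0.25/100 = 0.002375. For each clinic's six cell means, V = 0.0125·J + 0.002375·R. The plan takes R as the identity. Repeats put 0.6 × (share of patients in common) off the diagonal. The model SE is the treatment element of (Σ Z′W⁻¹Z)⁻¹, square-rooted, where W is V with R = I. The actual SE uses the sandwich form with the true V.

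| Overlap | Clinic-only model SE | Actual SE of that estimator |
|---|---|---|
| Same patients throughout | 0.0265 | 0.0170 |
| Overlap 0.7 to the power of the lag | 0.0265 | 0.0226 |
| Constant 40% overlap | 0.0265 | 0.0232 |

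Modelling the patient correlation in the first row gives 0.0168. Changing p rescales each row by the same factor and leaves the ratios alone. If patients recur only in the very next period (30% overlap), the two SEs nearly coincide (0.0265 and 0.0266). The size of the error therefore depends on how persistent the overlap is.

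**5. Effect on power.** Suppose instead that there are no repeats and visits are spread evenly. Cells at CHC1–3 are then 69.5, 53 and 88, and total N is 3,726 to 4,290. Under the plan's Hussey-Hughes model (difference 0.15, ICC 0.05, p = 0.5), power stays above 99.8%. Like the 2,000/2,800 split, this counts the implementation period as intervention time. Whether it should be excluded is a separate question.

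**The case against.** The best defence is that the harm runs in the safe direction. Under persistent overlap the planned SE is too large, so the test is conservative. Smaller cells leave power far above the stated 85% under the plan's own model. This stands, and it limits the severity. A reader might infer a lost or inflated result from the phrase wrong standard errors; the calculations do not support that.

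It can also be said that the article already calls the design an open cohort, and that unique may mean only that each survivor counts once per period. Both are fair. Neither rescues the expectation of few repeats, which Table 1 contradicts at CHC1–3.

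If clinic-period proportions are analysed, as parts of the Data analysis section suggest, no patient effect can be fitted, and the clinic random effect largely absorbs stable within-patient correlation. This stands too, so a patient random effect is not the only valid remedy.

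Three stronger readings are tempting and should not be drawn:

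- **The removal rule empties later cells of everyone already screened.** This needs positive to mean was screened. The text says such subjects are referred for treatment, which points to a test result, so few would be removed.
- **The removal rule flatly contradicts the EHR extraction section.** Extracting everyone seen and then applying an exclusion is coherent. The wording needs reconciling, but it is not a strict conflict.
- **CHC1–3 cannot reach 100 in a period.** They can, if patients seen in both halves of the year are counted twice. What Table 1 rules out is reaching 100 every period with few repeats.

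**Conclusion.** The point holds and should be fixed. At CHC1, CHC2 and CHC3, at least 31%, 47% and 12% of the planned observations must be repeats, and at least four of the eight clinics come from these systems. The 4,800 is therefore a count of patient-periods covering at most 3,726 to 4,290 distinct patients. This rests only on Table 1, read as distinct survivors per year (themselves estimates at 6.5% prevalence), and on the stated 100 per cell.

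The stated reason for making no adjustment does not apply to the primary outcome. That follows from the text alone.

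The effect on inference is less certain. At the assumed within-patient correlation of 0.6, ICC 0.05 and p = 0.5, a clinic-only patient-level model gives 0.0265 against about 0.017 to 0.023 under the persistent-overlap patterns examined. Intervals are then too wide. No loss of the stated power is shown.

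**What to change.** - Restate N as about 4,800 patient-period observations. Give the expected number of distinct patients and per-clinic cell sizes that agree with Table 1.
- Remove the claims of uniqueness and few repeats, and the positive/negative argument.
- Account for repeated patients in the primary analysis: a patient random effect if patient-level data are modelled, or an equivalent within-clinic correlation structure if clinic-period proportions are modelled.
- Define who is assessed in each period by eligibility for receipt of screening. Reconcile the exclusion of those who screened positive with the Outcomes and EHR extraction/audit sections.

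The cost is some rewording, a slightly more complex model, a re-run power calculation and a smaller stated number of distinct patients. No further data collection is needed, because the extracts already take every survivor seen. The analyst does need to be able to link a patient's records across periods within the de-identified data.

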
#### Secondary outcomes

We will conduct a cluster-adjusted two-sample t-test and/or mixed effect model to compare usual care and post-intervention outcomes. We will use a group (pre-/post- intervention) indicator as a fixed effect and a clinic-specific indicator as a random effect. We will also use a time-specific fixed effect. We will include a group*time interaction term to identify group-specific differential change in the secondary outcome between usual care and post-intervention time periods.

We will use graphical methods to examine variable distribution for outliers and abnormal values and verify statistical test assumptions using formal tests (e.g., Shapiro Wilks). We will utilize transformations or non-parametric methods to address any unmet assumptions. The clinic will serve as the unit of analysis. All tests will have a two-tailed alpha level of 0.05.

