#### Patient interviews

We will conduct patient interviews to elucidate experiences of care coordination and PCM domains: attitudes toward follow-up care; competing demands; and comprehension of clinic communications [40]. We will purposively sample patients to compare between clinics. Patient Surveys will measure the *Picker Patient Experience of Care care coordination subscale* and other potential confounders and effect modifiers [112, 113]. We. Surveys will be administered by phone during the pre- and then again during the post-intervention period. We have already translated these survey measures in Spanish, made them culturally appropriate, and understandable by individuals with low literacy (*R01CA203856*)*.*

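### The secondary outcomes may be tested by a t-test with no calendar-time term, so in this stepped wedge a background trend would be read as intervention effect

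*Protocol article*

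**What the plan says.** The Secondary outcomes section, under Data analysis, opens: "We will conduct a cluster-adjusted two-sample t-test and/or mixed effect model to compare usual care and post-intervention outcomes". It then describes the mixed model in three steps. The first sets the main terms: "We will use a group (pre-/post- intervention) indicator as a fixed effect and a clinic-specific indicator as a random effect". The second deals with calendar time: "We will also use a time-specific fixed effect". The third brings in an interaction: "We will include a group*time interaction term to identify group-specific differential change in the secondary outcome between usual care and post-intervention time periods". On the general rules for testing, the section states "The clinic will serve as the unit of analysis" and, for the significance level, "All tests will have a two-tailed alpha level of 0.05". It does not say how time is coded in the interaction, or which coefficient carries the test.

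The primary outcome is handled differently. The Data analysis section plans a mixed model with a clinic random effect, fixed period effects and one intervention indicator, without an interaction.

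The Outcomes section lists three secondary outcomes: survivorship knowledge and skills (survey), patients' experience of care coordination (survey), and adherence to surveillance guidelines. EHR data are extracted every six months. On the patient survey, the Patient interviews section says: "Surveys will be administered by phone during the pre- and then again during the post-intervention period".

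**The concern.** In a stepped wedge, clinics cross in one direction only, so usual-care data are early and intervention data are late. Exposure and calendar time are correlated by construction, and an analysis separates them only if it contains a time term. A two-sample t-test adjusted for clustering contains none. Any change that would have happened anyway, such as better documentation, new quality targets or growing clinician awareness, goes straight into its group difference.

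The *and/or* matters for two reasons. It allows the t-test to be the only analysis, and it leaves the choice between two analyses with different biases open until the data are in. At stake are the claims on clinician knowledge, care coordination and surveillance, any of which could be declared positive because of background change alone.

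**Working it through.** **1. Reproduce the plan's grid.** Randomization procedures gives 8 clinics, two crossing every six months, with the period during and after the intervention counted as treatment. Power calculation gives 100 × 8 × 6 = 4800, about 2000 under usual care and 2800 under intervention. If two clinics cross after each of periods 1 to 4:

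| Period | 1 | 2 | 3 | 4 | 5 | 6 | Total |
|---|---|---|---|---|---|---|---|
| Usual-care clinics | 8 | 6 | 4 | 2 | 0 | 0 | 20 |
| Intervention clinics | 0 | 2 | 4 | 6 | 8 | 8 | 28 |

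At 100 per cell this gives 2000 + 2800 = 4800, which matches the plan.

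**2. Calendar gap, implementation counted as treatment.**
- Usual care: (8×1 + 6×2 + 4×3 + 2×4)/20 = 40/20 = 2.00.
- Intervention: (2×2 + 4×3 + 6×4 + 8×5 + 8×6)/28 = 128/28 = 4.57.
- Gap: 2.57 periods × 6 months = 15.4 months.
- Within any one clinic, mean post period minus mean pre period is 3.0.

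**3. Calendar gap, 12-month implementation excluded.** Intervention cells are then 2, 4 and 6 clinics in periods 4, 5 and 6: (2×4 + 4×5 + 6×6)/12 = 64/12 = 5.33. The gap is 3.33 periods.

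**4. Spurious effect without a time term.** Spurious difference = gap × trend per period. The documents give no trend, so 1, 2 and 3 points per six months are assumptions:

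| Assumed trend (points per 6 months) | Pooled, gap 2.57 | Within clinic, gap 3.0 | Pooled, gap 3.33 |
|---|---|---|---|
| 1 | 2.6 | 3 | 3.3 |
| 2 | 5.1 | 6 | 6.7 |
| 3 | 7.7 | 9 | 10.0 |

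**5. False-positive rates at two-sided 0.05.** Assumptions: no intervention effect, base rate 0.5, ICC 0.01 to 0.05, 100 observations per clinic-period, implementation counted as treatment. The random-intercept row is a normal approximation; the t-test rows are simulations of 4,000 trials.

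| Comparison without time | 1 point | 2 points | 3 points |
|---|---|---|---|
| Random clinic intercept | 47–49% | 97% | about 100% |
| Clinic-level paired t-test | 37–38% | 88–90% | >99% |
| Clinic-level unpaired t-test, ICC 0.01 | 6% | 44% | 88% |
| Clinic-level unpaired t-test, ICC 0.05 | 0.3% | 4% | 18% |

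The unpaired test can reject rarely because between-clinic variation inflates its standard error. Its estimate is as biased as that of the paired test.

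**6. The same data with period effects.** With categorical period effects and one intervention indicator, the bias from a common trend is exactly 0 and the design matrix has full rank (7 of 7). At base rate 0.5 and ICC 0.05 the standard error is 0.026, against 0.015 without time terms. With implementation excluded it is 0.058 against 0.022.

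**7. The interaction.** A full categorical group-by-time model has 1 + 5 + 1 + 5 = 12 columns. Only 9 group-by-period combinations contain data: one in period 1, two in each of periods 2, 3 and 4, and one in each of periods 5 and 6. The rank is therefore 9, and a group contrast exists in periods 2–4 only. With linear time the model has full rank (4 of 4), as does group × linear time beside categorical periods (8 of 8). With implementation excluded, both conditions coexist only in period 4: the categorical model has rank 7 of 12, and the mixed coding has rank 7 of 8.

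**The case against.** The strongest reply is that the t-test is only the lesser option. The sentences after it set out a mixed model in some detail, and that model has a time effect. This is fair as to likely intent, but the text does not make the t-test subordinate or exclude it.

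Four stronger readings are tempting, and the document does not support them.

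- *That the mixed model also turns trend into effect.* It does not: "We will also use a time-specific fixed effect" answers this. The trend bias belongs to the t-test alone.
- *That the wedge cannot estimate the group-by-time term.* This is true only in part and only under some codings. With categorical time it is estimable in periods 2–4; with linear time, and implementation counted as treatment, it is estimable throughout. The article does not state the coding, and a fuller analysis plan may.
- *That the same people are surveyed twice and analysed as independent samples.* The sentence "Surveys will be administered by phone during the pre- and then again during the post-intervention period" places surveys in two periods but does not say that the same patients are contacted again. The trial is described as cross-sectional, and the Clinic survey section describes anonymous completion, so linkage may not be possible for staff if their survey is fielded in the same way.
- *That the 2.57-period gap applies to every secondary outcome.* The grid fits the six-monthly EHR extraction and so the surveillance outcome. Two of the three outcomes are surveys whose timing may differ. For these the direction holds, since post still follows pre, but the size is not established.

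**Conclusion.** The concern holds for the t-test. The plan permits a stand-alone comparison with no calendar-time term, in a design where intervention cells fall on average 2.57 periods (15.4 months) after usual-care cells, or 3.33 periods if implementation is excluded. The spurious pooled difference is about 2.6, 5.1 or 7.7 points for an assumed trend of 1, 2 or 3 points per six months at the smaller gap. The gap follows from the plan's own figures. The trend sizes, base rate and ICC values are assumptions, and the error rates depend heavily on which version of the t-test is used.

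The group-by-time term is a separate and smaller problem of interpretation. Once it is in the model, the group coefficient is no longer a single average intervention effect. If time is linear, it is the effect at whatever point is coded zero. If time is categorical with period 1 as reference, it is a contrast in a period with no treated clinic, so it depends on which terms the software drops. This is not a route by which trend becomes effect.

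**What to change.** - Delete the two-sample t-test as a permitted analysis of the secondary outcomes.
- Test each secondary outcome with the model planned for the primary outcome: fixed period effects, a clinic random effect and one intervention indicator, with the test on that indicator.
- Keep any effect-by-time term as exploratory only, and state its coding.
- Add a person effect only if respondents are in fact repeated and can be linked.

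This changes analysis wording only; the design stays as it is. Survey responses must be assignable to a calendar period. The statistical cost is wider intervals: under the assumptions above, the standard error rises by a factor of about 1.7 (0.026/0.015), or about 2.7 (0.058/0.022 before rounding) if implementation periods are excluded. That extra width is the uncertainty that the analysis without time terms leaves out.
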